### Participant timeline {13}

See Table 4.

**Table 4 Tab4:** Schedule of activities

	**Study months (± 2 weeks)** ^a^							
**Timepoint**	**Screening**	**On-treatment**					**Post-treatment**	
	** − 1**	**0**	**3**	**6**	**9**	**12**	**15**	**18**
**Enrolment**								
Eligibility screen “	X							
Informed consent	X							
Medical history and prior medication^b^	X							
Randomisation^c^	X							
**Interventions**								
**Pharmacological intervention**								
Placebo		X	X	X	X	X		
PIO		X	X	X	X	X		
SPIO		X	X	X	X	X		
SPIOMET		X	X	X	X	X		
**Lifestyle intervention** ^d^								
LIP and LIP-related questionnaires		X	X	X	X	X		
**Assessments**								
**Ovulation assessment** ^e^								
0–3 months—start		X						
0–3 months—stop			X					
9–12 months—start					X			
9–12 months—stop						X		
12–15 months—start						X		
12–15 months—stop							X	
**Clinical variables**								
Weight, height, BMI, WHR, SBP, DBP^f^		X	X	X	X	X	X	X
Hirsutism score		X	X	X	X	X	X	X
Acne score		X	X	X	X	X	X	X
Menstrual regularity		X	X	X	X	X	X	X
**Endocrine-metabolic variables**								
Circulating androgens^g^		X		X		X		X
Lipids^g^		X		X		X		X
Fasting insulin and glycaemia^h^		X	X^h^	X	X^h^	X	X^h^	X
Glucose-stimulated insulinaemia (OGTT)^i^		X				X		X
Markers of inflammation & insulin sensitivity^g^		X		X		X		X
**Epigenetic variables**								
Circulating miR-451a concentrations		X		X		X		X
**Imaging variables** ^j^								
Cardiovascular risk: cIMT (ultrasound)		X				X		X
Body composition: DXA		X				X		X
Abdominal fat distribution and hepatic fat: MRI		X				X		X
**Adherence and acceptability**								
Adherence to treatment		X	X	X	X	X		
Acceptability of the tablet			X			X		

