#### Criteria for discontinuing or modifying allocated interventions {11b}

Study participants are free to withdraw from participation at any time upon request.

Discontinuation of the study intervention will imply discontinuation of the study and thus a dropout, so that any remaining study procedures will not be performed.

All data available until the discontinuation of the study intervention will be collected. If a clinically relevant finding is identified (including, but not limited to changes from baseline) after enrolment, the investigator or qualified designee will determine whether any change in participant management is needed. Any new clinically relevant finding will be reported as an adverse event (AE).

Criteria for discontinuing the allocated intervention are as follows: (1) pregnancy; (2) significant non-compliance with the intervention, for example, no medication intake for 30 consecutive days; in case of AE, patients are allowed to interrupt the treatment for 7 days without being withdrawn from the study; (3) any clinical AE, laboratory abnormality, or other medical condition/situation such that continued participation in the study is unlikely to be in the best interest of the participant; (4) appearance of an exclusion criterion (either newly developed or not previously recognised).

In case of premature termination of study participation, the patient will be re-allocated to the outpatient clinic as a regular patient whenever possible.

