#### Strategies to improve adherence to interventions {11c}

A face-to-face medical visit will be scheduled every 3 months for each participating AYA, for a total of 5 visits over 12 months to maintain a close contact, and to monitor adherence until the end of the active treatment phase. Adherence will be calculated as the ratio between the number of tablets prescribed and dispensed for the period between hospital appointments and the number of tablets returned by the patient at the following appointment. In addition, the Intake Table of the Patient Diary will be screened to check whether the aforementioned ratio fits with the information registered by the patient.

The aforementioned LIP sessions will be implemented by a trained research nurse during the same 5 quarterly visits over the same 12 months of active intervention [77]. In order to optimise adherence, the LIP will focus on strengths rather than on weaknesses; such an approach is known to raise treatment adherence [80].

In order to further improve adherence to the pharmacological and LIP interventions, patients will be contacted by phone between clinical visits, in order to check how they are doing.

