Baseline (time 0), on-treatment (3, 6, 9 and 12 months) and post-treatment (15 and 18 months) evaluations.Saliva samples for ovulation assessment (by progesterone measurement) will be collected weekly between 0 and 3 months (for 12 consecutive weeks during months 1, 2 and 3), between 9 and 12 months (for 12 weeks during months 10, 11 and 12) and between 12 and 15 months (for 12 weeks during months 13, 14 and 15).Clinical features will be collected at each time point (height and weight to infer BMI; waist and hip circumference to infer WHR; SBP and DBP; hirsutism and acne scores; menstrual regularity) besides information on concomitant medication and adverse events.At time 0, 6, 12 and 18 months, blood sampling will be performed in the fasting state to assess endocrine-metabolic, epigenetic and laboratory safety variables. At time 0, 12 and 18 months, additional blood sampling will be performed after 2 h of glucose upload for insulin and glycaemia assessment. At time 3, 9 and 15 months, blood sampling (for fasting insulin and glycaemia assessment) will be performed only in the event of clinically relevant hyperglycaemia observed at any time in the prior months.At time 0, 12 and 18 months, ultrasound, DXA and MRI will be performed for assessments of respectively cIMT, body composition, and partitioning of abdominal fat, including hepatic fat.Adherence to treatment will be assessed at each time point from baseline to time 12 months; whereas acceptability of the tablet will only be recorded at time 3 and 12 months.A highly sensitive serum or standard sensitive urine pregnancy test will be performed at each time point from baseline to time 12 months.At each time point from baseline to time 12 months, will attend to a LIP session, and fill in LIP-related questionnaires.At time 0, 6, 12 and 18 months, PROMs on HRQoL will also be assessed.Between hospital visits throughout the 18 months of study, the participants will record—in a diary—their menses, the time of any medication intake and any adverse event. Participants will deliver this diary at the next visit.At time 0 and 18 months, an online survey will collect information on the patient’s experience, respectively, during the enrolment process and throughout the 18 months of the actual study.

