##### Adherence and acceptability

*Adherence:* as a marker of adherence to intervention, the ratio will be calculated (and expressed in %) between the number of tablets that were ingested and those that were prescribed, the former being calculated as the difference between the number of tablets that were dispensed and those that were returned at the subsequent visit. In addition, the Intake Table of the Patient Diary will be screened to check whether the calculated ratio (or %) fits with the information registered by the patient.
*Acceptability of the tablet:* the patient’s opinion regarding the palatability and easiness to swallow the tablet (containing Placebo, PIO, SPIO or SPIOMET) will be recorded by using a simple questionnaire with numerical rating scales, adapted from reference [105] and shown at Table 6.

**Table 6 Tab6:** Tablet acceptability questionnaire

Numerical Rating Scales (NRSS) OR qualitative/descriptive controlled vocabulary for palatability/acceptability assessments of paediatric oral use formulations					
**Score**	**1**	**2**	**3**	**4**	**5**
Overall opinion of taste	Very bad	Bad	Acceptable/ OK/ Not nice and not bad	Good/ Nice	Very good/ Very nice
Overall swallowability (descriptive)	Vomits the drug immediately or within 2 h	Spat it out	Swallowed with some problems	Swallowed with no problems	
Parent/caregivers’ overall opinion on their daughter’s acceptability of the formulation	Very bad	Bad	Acceptable/ OK	Good	Very good

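### Tablet acceptability is rated only at months 3 and 12, and nobody is rated after stopping, so the scores are liable to upward bias: probably small at month 3, possibly larger at month 12

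*Protocol article*

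**What the plan says.** Acceptability is listed among the secondary outcomes. It is measured with the short Table 6 questionnaire, which covers taste, swallowability and the caregiver's opinion. Table 4 marks the row "Acceptability of the tablet" at months 3 and 12. The section on collection of outcomes agrees: "acceptability of the tablet will only be recorded at time 3 and 12 months".

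Section {11b} treats a patient who stops the tablet as "thus a dropout, so that any remaining study procedures will not be performed". It adds that "All data available until the discontinuation of the study intervention will be collected", but no acceptability rating falls due before month 3. The grounds for stopping include adverse events, the patient's own wish, and "significant non-compliance with the intervention, for example, no medication intake for 30 consecutive days". After an adverse event, "patients are allowed to interrupt the treatment for 7 days without being withdrawn from the study".

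The lowest of the four swallowability grades is "Vomits the drug immediately or within 2 h", and the next is spitting the tablet out. Section {11c} states that "patients will be contacted by phone between clinical visits, in order to check how they are doing".

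The background section puts metformin's gastrointestinal effects, nausea and vomiting among them, above 10% and says they usually settle soon after treatment begins. Table 3 shows metformin in the SPIOMET arm only.

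**The concern.** Whether a rating exists depends on staying on the tablet, and staying on it may depend on what the rating would have been. A patient who vomits the tablet, spits it out or finds it intolerable is more likely to stop than one who takes it easily. If she stops in the first three months she contributes nothing to this outcome. Missing ratings are then related to the quantity being measured, and an average over the patients who were rated would be too favourable.

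The arms could also be affected unequally. The expected early gastrointestinal effects belong to one component, in the arm the trial is mainly meant to evaluate, and the first rating comes after the period in which those effects are most expected. What is at stake is the reading of one secondary outcome, although an age-appropriate tablet is part of the trial's purpose.

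**Working it through.** **Plan's own figure.** The article gives no acceptability figure to reproduce. The related figure is the number of completers: 364 × (1 − 0.27) = 265.7, which matches the stated 266. The 27% is split neither by time nor by cause.

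**Timeline.** Table 4 sets a month at 30 days with a window of ± 2 weeks, so the month-3 visit is day 90 (days 76 to 104).
- A patient with no intake from day 0 reaches the 30-day example on day 30, which is 60 days before the visit (46 to 74 with the window).
- A run of no intake starting after about day 60 (46 to 74) does not reach 30 days before the visit, so that patient can still be rated.
- The gap does not depend on the 30-day example. Voluntary withdrawal or a stop for an adverse event before month 3 leaves the same missing rating.

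**Share without a rating.** Assume a constant hazard reaching 27% at 18 months: D(t) = 1 − 0.73^(t/18).
- Month 3: D = 1 − 0.73^(3/18) = 5.1%, or 0.051 × 91 ≈ 5 patients per arm.
- Month 12: D = 1 − 0.73^(12/18) = 18.9%, or 0.189 × 91 ≈ 17 patients per arm.
- A straight-line dropout gives nearly the same: 27% × 3/18 = 4.5% and 27% × 12/18 = 18%.

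**Size of the overstatement.** Let q be the share rating the tablet acceptable among those rated (assumed 90%). Let s be the share of dropouts caused by the tablet, all of whom would have rated it unacceptable (assumed). Patients who drop out for other reasons are left out of the denominator.

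Share acceptable with tablet-related stoppers included = q(1 − D) / [(1 − D) + sD]

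Example, month 12, s = 50%: 0.9 × 0.811 / (0.811 + 0.095) = 80.6%, so 90% is overstated by 9.4 points.

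| s | Month 3 (D = 5.1%) | Month 12 (D = 18.9%) |
|---|---|---|
| 10% | 0.5 points | 2.1 points |
| 25% | 1.2 points | 5.0 points |
| 50% | 2.4 points | 9.4 points |
| 100% | 4.6 points | 17.0 points |

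Earlier dropout would raise these figures. If the whole 27% had left by month 12, the month-12 column would run from 3.2 to 24.3 points. A rating from every patient who stops would bring this source of error to zero.

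**The case against.** The strongest reply is that few patients are likely to be affected and that most poor raters will still be asked. Bad taste, difficult swallowing and irregular intake trigger no withdrawal, and the tablet may be broken. Tablet counts and diaries are reviewed at the next visit, so a patient who stopped silently may be discovered at month 3, when the questionnaire is due. Vomiting and intolerance are also recorded as adverse events. The article describes side effects as essentially absent at these low doses, which weakens the metformin argument. An early-termination form could sit in the full protocol.

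Much of this stands. It is why the month-3 effect is probably small and why low scores remain possible there. It does not close the gap. Adverse event reports do not supply a Table 6 score. A patient found at month 3 to have stopped falls under the rule that ends her procedures. The article's own wording, which limits the ratings to two time points and ends procedures at discontinuation, points against a rating at withdrawal.

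A reader might infer more than the text supports:
- *Patients who cannot tolerate the tablet are withdrawn by rule.* Section {11b} does not say so. The 30 days is an example of no intake, and a tablet that is swallowed and vomited, or spat out, is not clearly no intake.
- *The size of the tablet biases the comparison between arms.* All four tablets have the same size, shape and colour, so difficulty from size is equal by design. Only taste or drug effects could differ.
- *Adherence suffers in the same way.* The diary records each intake, and data up to discontinuation are collected. Percentage of planned doses, including time after stopping, is a different quantity from adherence while on treatment.

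**Conclusion.** The point holds in limited form. The two rating times and the end of procedures at discontinuation are explicit, and together they leave early stoppers without any rating and later stoppers without a month-12 rating. Tablet-related stopping is plausible, so the scores are liable to upward bias. The documents do not show that bias will occur, nor that only patients who tolerate the tablet are rated.

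The illustrated overstatement is about 0.5 to 5 points at month 3 and 2 to 17 points at month 12. It rests on three assumptions: a constant hazard to 27%, 90% acceptable among those rated, and 10% to 100% of dropouts being tablet-related. The upper ends need every dropout to be caused by the tablet. A difference between arms is possible through metformin's early effects, but its size cannot be derived. This is a cheap improvement to one secondary outcome and leaves the primary analysis untouched.

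**What to change.** In Table 4 and in the text on collection of outcomes, keep months 3 and 12 and add the Table 6 questionnaire at two points:
1. An early between-visit phone call, with its timing fixed within the first treatment interval. Such calls are already planned in section {11c}.
2. The contact at which a patient discontinues the tablet, whatever the reason. Section {11b} should state that this rating belongs to the data collected up to discontinuation, so that it does not conflict with the end of procedures.

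Report acceptability in all patients who took at least one tablet, and show the number of tablet-related withdrawals by arm next to the scores.

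The cost is one or two more short questionnaires per patient, an added entry in the schedule, and possibly less favourable acceptability figures. No treatment or stopping criterion changes.

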**Safety variables**								
Laboratory safety variables^k^		X		X		X		X
Pregnancy test^l^		X	X	X	X	X		
Adverse events reporting^m^		X	X	X	X	X	X	X
**PROMs on HRQoL** ^n^								
SF-36		X		X		X		X
PCOSQ		X		X		X		X
**Other activities**								
Concomitant medication^o^		X	X	X	X	X	X	X
Patient diary			X	X	X	X	X	X
Online survey (optional)^p^		X						X

^a^1 month is equal to 30 days. Total duration of the clinical study per patient (including 12 months on-treatment and 6 months post-treatment): 18 months

“To verify the inclusion/exclusion criteria, the following parameters will be measured: body mass index (BMI), gynaecological age, hirsutism, acne, menstrual regularity, blood count (haemoglobin, haematocrit, red blood cell count, white blood cell count, platelet count), electrolyte panel (sodium, potassium, chloride, calcium, phosphorus), lipids [total cholesterol, low-density lipoprotein (LDL-cholesterol), high-density lipoprotein (HDL-cholesterol), triglycerides], glucose, insulin, alanine transaminase (ALT), aspartate transaminase (AST), gamma-glutamyltransferase (GGT), creatinine, urea, vitamin B12, folic acid, progesterone, 17-OH-progesterone, thyroid-stimulating hormone (TSH), androgens [testosterone, sex hormone binding globulin (SHBG), free androgen index (FAI), androstenedione, dehydroepiandrosterone-sulphate], prolactin, ultra-sensitive human chorionic gonadotropin (us-HCG). Androgens will be measured in the early follicular phase of the cycle (days 3 to 7) or after 2 months of amenorrhea

^b^Medical history including any clinically significant event during the past 5 years. Only prior medication relevant for in/exclusion criteria and/ or PCOS will be collected

^c^The screening period finalises with randomisation. All patients will be randomised before the basal visit (month 0), including performing any analyses/test related to this visit

^d^A trained research nurse will lead lifestyle intervention in a quarterly session through a Lifestyle Intervention Programme (LIP) and LIP-related questionnaires [self-reported Health Behaviour questionnaire, SCOFF & first question from Binge Eating Disorder Screener 7 (BEDS-7), Eating Disorder Examination Questionnaire EDE-Q (only in case the risk is confirmed)]. Patients can be contacted to check their status by phone between the visits at site

^e^By weekly salivary progesterone measurements for 12 consecutive weeks in three periods

^f^
*BMI* Body mass index, *WHR* Wwaist-to-hip ratio, *SBP* Systolic blood pressure, *DBP* Diastolic blood pressure

^g^Circulating androgens: total testosterone, sex hormone-binding globulin (SHBG), free androgen index (FAI), androstenedione. Lipids: total cholesterol, low-density lipoprotein (LDL-cholesterol), high-density lipoprotein (HDL-cholesterol), triglycerides. Markers of inflammation and insulin sensitivity: ultra-sensitive C-Reactive protein (us-CRP), C-X-C motif chemokine ligand-14 (CXCL14), high-molecular-weight adiponectin (HMW-adip), growth-and-differentiation factor 15 (GDF15)

^h^At visit months 3, 9 and 15, these analyses are to be performed only when they are necessary, namely in the event of clinically relevant hyperglycaemia observed at any time point. For patients with normal glycaemic status, these analyses are not required

^i^
*OGTT*, oral glucose tolerance test. Fasting and 2 h after an oral glucose load

^j^
*cIMT*, carotid intima media thickness; *DXA*, dual X-ray absorptiometry; *MRI*, magnetic resonance imaging

^k^Laboratory safety variables: blood count, electrolyte panel (sodium, potassium, chloride, calcium, phosphorus), alanine transaminase (ALT), aspartate transaminase (AST), gamma-glutamyltransferase (GGT), creatinine, urea, vitamin B12 and folic acid

^l^Highly sensitive serum or standard sensitive urine pregnancy tests

^m^The study clinician or designee team member will record all reportable events from treatment start until 6 months post-treatment

^n^
*PROMs*, patient-reported outcomes; *HRQoL*, health-related quality of life; *SF-36*, short-form 36 health survey; *PCOSQ*, PCOS health-related quality of life questionnaires

^o^Concomitant medication should include both, prescription and over-the-counter medications taken by the patient throughout the study period, including dose, frequency, indication, start and stop dates

^p^Optional survey to answer questions about the study conduct

### Sample size {14}

Numbers of patients in the four study arms have been calculated to attain 80% statistical power at two-sided 5% alpha level [90–92], with an expected dropout rate of 27%. The sample size is based on the two-sample *t*-test (R package “pwr”, functions “pwr.t.test” and “pwr.t2n.test”).

The number of subjects to be included has been determined based on the primary endpoint, namely the number of ovulations over 6 months (from month 9 to month 15). This design will cover to detect a 0.922 mean difference between placebo and SPIOMET arms. The standard deviation of 1.96 is based on previous evidence [14, 15]. The same difference and standard deviation are considered for potentially subsequent hierarchical comparisons (see the section “Trial design {8}”).

A sample size of 364 AYAs with PCOS [at least 180 of whom will be aged < 18.0 years at study start] is required using a 1:1:1:1 allocation ratio for placebo, PIO, SPIO and SPIOMET. The number of participants to be recruited is thus 91 per treatment arm (Table 5). Assuming a 27% dropout rate, approximately 266 patients (~ 66 or 67 per treatment arm) are estimated to complete the study.

**Table 5 Tab5:** Sample size and minimum detectable differences among comparison groups

Allocation ratio	1:1:1:1	

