## Trial design {8}

This is a multi-centre, multi-national, randomised, double-blind, placebo-controlled, four-arm parallel group, phase II clinical trial, with 1:1:1:1 allocation ratio. A total of 364 AYAs with PCOS will be randomly assigned to receive:Placebo (*N* = 91)PIO 7.5 mg (*N* = 91)SPI 50 mg + PIO 7.5 mg (SPIO, *N* = 91)SPI 50 mg + PIO 7.5 mg + MET 850 mg (SPIOMET, *N* = 91)

Patients belonging to the four different subgroups will ingest a tablet once daily at dinner time over 12 months and will be followed for another 6 months post-treatment. In addition, all patients will receive the same lifestyle guidance throughout the active treatment phase.

The analysis will be conducted following a hierarchical approach. The multiplicity will be fully controlled, and the alpha level will be therefore maintained at a predefined two-sided 5% level. A fixed-sequence statistical strategy has been planned to test treatment groups in a predefined order, all at the same significance level alpha (e.g. *α* < 0.05), moving to a next comparison only after a statistically significant difference on the previous comparison (https://www.fda.gov/media/102657/download). The following predefined order has been planned:Placebo vs SPIOMETPlacebo vs SPIOPlacebo vs PIOPIO vs SPIOMETSPIO vs SPIOMET

In this hierarchical approach, the first comparison will be analysed as first, and the next comparison will be analysed only if there is a statistically significant finding for the first comparison (*p* < 0.05). Hence, if there is no significant finding for the first comparison, no formal statistical conclusion can be reached for the subsequent comparisons (2nd, 3rd and 4th), even if there is a large apparent treatment effect. Therefore, the 5th comparison will only be declared as statistically significant, if the previous 1st, 2nd, 3rd and 4th comparisons were to achieve the significant criteria (*p* < 0.05).

Patients will be randomised (1:1:1:1) with stratification by:Clinical site: 7 sitesGynaecological age (years elapsed since menarche): 2–5 years and > 5 yearsBMI: < 24.9 and ≥ 25.0 kg/m^2^

Additionally, patients will be allocated with a minimisation method (including an element of randomisation) (https://www.fda.gov/media/87621/download).

The trial has been registered in EudraCT under the ID 2021–003177-58 and Clinicaltrial.gov under the ID NCT05394142. The Ethics Committee (EC) of all participating clinical centres approved the trial.

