**Sample size**		
**Total**	**364**	
Placebo	91	
PIO	91	
SPIO	91	
SPIOMET	91	
	**Minimal detectable mean differences** ^a^ ** and common standard deviations**	**Power** ^b^
1. Placebo vs SPIOMET	0.922 (1.96)	80%
2. Placebo vs SPIO	0.922 (1.96)	64%
3. Placebo vs PIO	0.922 (1.96)	51%
4. PIO vs SPIOMET	0.922 (1.96)	41%
5. SPIO vs SPIOMET	0.922 (1.96)	33%

^a^For ovulation rates

^b^Power to detect statistically significant differences within a fixed-sequence multiple testing approach

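### Table 5 gives all five comparisons the same 0.922 difference, which four arm means cannot satisfy; at the planned SPIOMET effect, power for comparisons 4 and 5 is about 1% to 6%, not 41% and 33%

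*Protocol article*

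**What the plan says.** The protocol article, under Sample size {14}, sets the target as "to attain 80% statistical power at two-sided 5% alpha level" and bases it on a two-sample t-test. On the effect: "This design will cover to detect a 0.922 mean difference between placebo and SPIOMET arms". On the spread: "The standard deviation of 1.96 is based on previous evidence". For the later tests: "The same difference and standard deviation are considered for potentially subsequent hierarchical comparisons".

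Table 5 puts these inputs into five rows, each showing 0.922 (1.96):

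| Comparison | Stated power |
|---|---|
| 1. Placebo vs SPIOMET | 80% |
| 2. Placebo vs SPIO | 64% |
| 3. Placebo vs PIO | 51% |
| 4. PIO vs SPIOMET | 41% |
| 5. SPIO vs SPIOMET | 33% |

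Footnote b defines the last column: "Power to detect statistically significant differences within a fixed-sequence multiple testing approach". The gatekeeping rule is under Trial design {8}: "the 5th comparison will only be declared as statistically significant, if the previous 1st, 2nd, 3rd and 4th comparisons were to achieve the significant criteria". On numbers, the sample size section says "The number of participants to be recruited is thus 91 per treatment arm", with 27% dropout leaving 66 or 67 completers per arm. No set of four arm means is given.

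**The concern.** Differences between arm means add up. Row 1 fixes SPIOMET against placebo and row 3 fixes PIO against placebo, so together they determine SPIOMET against PIO, and row 4 is not free to take its own value. Rows 1 and 2 determine row 5 in the same way. A cumulative power through a sequence of tests describes one state of the world. If that state does not exist, the power has no meaning.

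Comparisons 4 and 5 are the only formal tests of whether SPIOMET improves on PIO or on SPIO. A chance of 33% to 41% describes a secondary question that the trial may well fail to answer. A chance of a few per cent says that, at the planned effect, the trial is almost certain not to answer it by testing. Anyone interpreting a failed step 4 or 5 needs to know which of these applies.

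**Working it through.** **Inputs (Sample size {14}, Table 5, Trial design {8}).** Difference 0.922; SD 1.96; two-sided alpha 0.05; two-sample t-test; 91 randomised and 66 or 67 completers per arm; the five tests in the order above, each reached only if all earlier ones are significant.

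**1. Reproduce row 1.** Exact two-sample t-test power has 2n − 2 degrees of freedom and noncentrality (0.922/1.96) × √(n/2).

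| n per arm | Noncentrality | Power |
|---|---|---|
| 66 | 2.702 | 76.5% |
| 67 | 2.723 | 77.1% |
| 72 | 2.822 | 80.05% |
| 91 | 3.173 | 88.4% |

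The article does not state 72 per arm. It is the size at which 0.922 gives 80%. Because the size behind the table is not stated, results below are shown for 66, 72 and 91.

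**2. Reproduce rows 2 to 5.** 0.80² = 0.640, 0.80³ = 0.512, 0.80⁴ = 0.410, 0.80⁵ = 0.328. These round to the stated 64/51/41/33%. The column therefore assumes that every step has 80% power at its own true 0.922, and that the five tests are independent although they share the placebo and SPIOMET arms.

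**3. Test whether the five rows can coexist.** Set the placebo mean to 0.
- Row 1: SPIOMET = 0.922. Row 3: PIO = 0.922. Then SPIOMET − PIO = 0.922 − 0.922 = 0, not the 0.922 of row 4.
- Row 2: SPIO = 0.922. Then SPIOMET − SPIO = 0, not the 0.922 of row 5.
- Letting signs differ gives 0.922 − (−0.922) = 1.844. Only 0 and 1.844 are possible, never 0.922.

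**4. Joint power under coherent arm means.** Four normal arm means with SD 1.96 were simulated (1,000,000 trials per scenario), with the five shared-arm t-tests counted cumulatively and significance required in the superiority direction. Means are relative to placebo, in the order PIO, SPIO, SPIOMET.

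| Arm means | n per arm | Cumulative power, comparisons 1 to 5 |
|---|---|---|
| 0.922, 0.922, 0.922 | 66 | 76 / 64 / 56 / 0.7 / 0.2% |
| 0.922, 0.922, 0.922 | 72 | 80 / 69 / 61 / 0.9 / 0.2% |
| 0.922, 0.922, 0.922 | 91 | 88 / 81 / 75 / 1.3 / 0.3% |
| Even steps: 0.307, 0.615, 0.922 | 72 | 80 / 43 / 12 / 2.3 / 0.8% |

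**5. Best case with SPIOMET − placebo held at 0.922.** A grid over the PIO and SPIO means (100,000 trials per point) gives the largest cumulative power for each comparison separately:

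| n per arm | Comparison 4 | Comparison 5 |
|---|---|---|
| 66 | about 2.5% | about 0.8% |
| 72 | about 3% | about 1% |
| 91 | about 6% | about 2% |
| Stated | 41% | 33% |

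The maximum is low because the sequence needs PIO to beat placebo and also to be beaten by SPIOMET, inside a total gap of 0.922. With PIO halfway, at 0.461, each of those two tests on its own has only about 29% power at 72 per arm. The two also pull against each other, because a high observed PIO mean helps the first and hurts the second.

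**6. What the stated 41% and 33% would need.** At 72 per arm, PIO = SPIO = +0.85 and SPIOMET = +1.70 gives 41% and 33%, but row 1 is then above 99%. PIO = SPIO = +0.922 and SPIOMET = +1.844 makes rows 2 to 5 all 0.922 and gives 53% and 45% at 72 per arm (47% and 39% at 66), again with row 1 near 100%.

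**The case against.** **The rows are separate detectable differences.** Table 5 heads its column as minimal detectable mean differences. With equal arm sizes and a common SD, such a threshold is the same for every pair, so 0.922 five times would be correct. This stands for the difference column read alone. It does not save the power column, because footnote b makes that a probability within the fixed sequence, which needs all the effects to hold at once.

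**A larger SPIOMET effect is possible.** The article's rationale is additive benefit, so a stepwise pattern ending well above 0.922 is not far-fetched. A reader might therefore infer from the algebra that powers of 41% and 33% can never arise. The documents do not support that reading: step 6 shows patterns that give them. What those patterns cannot do is agree with row 1, which states 0.922 and 80%. The ceilings in step 5 hold only on that condition.

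**Arm size.** A ceiling of 3% and 1% assumes 72 per arm. The article plans to analyse all randomised patients with imputation, so 91 can be argued, and the ceiling is then about 6% and 2%. This is a fair limit on the figure and leaves the conclusion unchanged.

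**Independence.** Ignoring the shared arms does not inflate every row. With all actives at +0.922, the stated 64% and 51% for comparisons 2 and 3 are conservative (about 69% and 61% at 72 per arm).

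**Consequences.** A reader might infer that funders or regulators were misled, or that the plan would treat non-significance as no added benefit. Nothing in the article shows either. Trial design {8} says that a failed step allows no formal conclusion on later ones, and the statistical methods section already promises point estimates and 95% confidence intervals. The primary sizing, which rests on comparison 1, is also unaffected by this error.

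**Conclusion.** The concern holds as a misstated power table. No set of four arm means satisfies Table 5, and its power column is 0.80 multiplied by itself. If SPIOMET exceeds placebo by the stated 0.922, cumulative power for comparisons 4 and 5 is at most about 2.5% and 0.8% (66 per arm) to 6% and 2% (91 per arm), against 41% and 33%. Comparison 4 is therefore overstated roughly sevenfold or more, and comparison 5 by more than that.

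The algebra in step 3 needs no assumption beyond the table. The size of the overstatement rests on SD 1.96, normal arm means, two-sample t-tests, and SPIOMET minus placebo fixed at 0.922. If the sponsor in fact expects a SPIOMET effect nearer 1.7, powers close to those stated are attainable for comparisons 4 and 5, but then row 1 and the sizing statement describe a different trial. The error lies in what the protocol reports. It does not touch alpha control, and the sizing of comparison 1 does not depend on it.

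**What to change.** Replace rows 2 to 5 of Table 5 with simulated joint power under one or two explicit, coherent sets of four arm means, allowing for the shared arms. Suitable sets are all actives at +0.922, and a stepwise increase with the assumed SPIOMET effect stated. Give the number per arm used in the calculation.

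Add a sentence along these lines: at the planned SPIOMET–placebo difference of 0.922, comparisons 4 and 5 have almost no power within the fixed sequence and will be interpreted mainly through estimated differences and 95% confidence intervals; a non-significant or untested result is not evidence of no added benefit.

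The cost is one simulated table and a sentence. Arms, sample size, order of tests and conduct do not change. The only loss is that the stated powers for comparisons 4 and 5 become much less favourable.
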